**Figure 1 fig-1:**
[figure not shown]
Flowchart of trial procedures.

### Participants

Participants will be community-dwelling, co-residing dyads of people living with dementia and their primary caregiver (see Table 2 for how caregivers were operationalised) in Australia and New Zealand. Table 2 lists inclusion and exclusion criteria. Participants will not be restricted in receiving any usual care for health (including mental health) conditions. Given the feasibility nature of the current study and the prevalence of medication usage in our target population, we will not exclude participants taking medication known to affect sleep. Broad inclusion criteria were set due to the feasibility nature of the trial; assessment of characteristics of responders (*i.e.,* type/severity of dementia diagnosis) and other considerations may be undertaken to aid the development of a future randomised controlled trial.

**Table 2 table-2:** Inclusion and exclusion criteria at allocation.

	People living with dementia	Caregivers
Inclusion	1. Living with dementia (any type) 2. Receive overnight support from a caregiver at least three nights per week 3. Ability to provide informed consent, or provide assent to their caregiver 4. Endorsed sleep concerns as rated “*Yes*” on a single-item^*^ by their primary caregiver	1. Living with and supporting a person with dementia at least three nights per week 2. Ability to communicate in English 3. Regular access to phone, email, and internet 4. Obtain scores of five or more on the Pittsburgh Sleep Quality Index
Exclusion	a) Living in a residential care home b) Have severe, untreated medical or physical health conditions that directly and significantly impact sleep (*e.g.*, severe pain, emphysema) c) High risk of harm to self/others	a) Report a diagnosis of schizophrenia, bipolar disorder or posttraumatic stress disorder b) Have severe, untreated medical or physical health conditions that directly and significantly impact sleep (*e.g.*, severe pain, emphysema) c) Undertake fixed night shift work between midnight and 5am, or rotating work schedules that require night shifts during participation d) Report a diagnosis of narcolepsy e) High risk of harm to self/others

**Notes.**

* The single item assessing sleep concerns in people living with dementia is: “*Do you think that sleep is an issue in the person you’re supporting?*”.

### Procedure

#### Recruitment

The trial is referred to as the “Dementia, Sleep and Wellbeing Study” and will involve varied recruitment methods. Information about the trial will be made available on the Dementia Australia and StepUp for Dementia Research websites. Dementia and caregiver support groups will be approached to share information with members. Project information and the accompanying link to the online explanatory statement is posted on Facebook caregiver and dementia support groups in Australia and New Zealand. Flyers are also placed in community centres and medical practices.

#### Informed consent

Recommendations from the UK Alzheimer’s Society (Alzheimer’s Society, 0000) for obtaining informed consent from people living with dementia will be followed. The link to the explanatory statement first asks potential participants to select one of two options (“I am a person living with dementia” or “I am a carer for someone living with dementia”) after which they will be directed to the appropriate explanatory statement (*i.e.,* one for people with dementia or one for caregivers). This will include information about assessments, the intervention, research procedures, potential risks, reimbursement, confidentiality and freedom to withdraw. After reading the explanatory statement, participants will complete a consent form (see Supplementary) and provide contact details. Caregivers will be asked whether they believe the person they are supporting will be able to provide informed consent or assent during initial screening questions (detailed below). Consent/assent will be re-confirmed during a telephone call with both the caregiver and person living with dementia.

#### Screening and risk assessment

Following consent, participants will be directed to an online form to complete brief screening questions which assesses initial eligibility criteria (*e.g.*, for caregivers: “*Do you have current mental health conditions [*e.g.*, schizophrenia, bipolar disorder, PTSD] that directly impact sleep?*”). If exclusion criteria have not been met, participants will be contacted *via* email to schedule a telephone call. Participants who meet exclusion criteria following screening questions will be contacted to confirm ineligibility.

In the screening telephone call, author AB, a provisional psychologist, will: (a) explain the purpose and details of the project and intervention; (b) confirm participants’ interest to participate; (c) assess caregiver sleep disturbance *via* Pittsburgh Sleep Quality Index (PSQI; Buysse et al., 1989) and sleep disturbance in the person with dementia through the Sleep Disorders Inventory (SDI; Tractenberg et al., 2003); (d) provide details of questionnaires (*i.e.,* format and expected duration of roughly 15–20 min); (e) discuss capacity of the person with dementia to complete questionnaires (people with dementia will be encouraged to complete assessment materials if they, or their caregiver, report capacity to do so) and; (f) conduct a risk assessment.

The risk assessment is undertaken to assess any risk of harm to self and others (*i.e.,* suicidal/homicidal ideation, plan, intent, and previous risk behaviours). Those deemed as high risk are referred to appropriate clinical mental health services and are ineligible to participate; any risk-related issues are discussed with authors SV and MJ (both psychologists), and an external clinical psychologist (described later). Those deemed ineligible to participate after the screening telephone call will be provided a comprehensive list of external support services and excluded from the trial.

#### Intervention

After screening, eligible participant dyads will participate in a 20-minute “pre-orientation” session *via* video with a trained research assistant to explain use of actigraph and sleep diary, which are sent *via* post prior to predetermined start date. Participants will complete an online baseline questionnaire within a week prior to beginning the intervention; automatic prompts to complete all items will be provided, and email reminders will be sent if questionnaires have not been completed within five days of release*.* Eligible participants will receive the intervention as detailed below. Participants will wear an actigraph and complete sleep diaries daily for two weeks prior to intervention start date, and then return the watches and diaries to the research team to be downloaded and recharged. The actigraphs and new diaries will be posted to be worn again during Weeks 5 and 6 of the intervention. A trained research assistant will manage actigraph recharging and monitor data. Sleep diaries and actigraphs are returned following completion of the follow-up questionnaire (Week 10). Ethics approval will be sought by Monash University Human Research Ethics Committee for any protocol modifications before being implemented and communicated to participants if appropriate, and will be documented on a running sheet.

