**Notes.**

T0 Pre-study screening/consent and baseline

T1 Time-point 1 (Week 0) pre-intervention baseline questionnaire undertaken within one week of intervention start

T2 time-point 2 (Week 6) post-intervention

T3 Time-point 3 (Week 10) follow-up

X Undertaken at that time point

SF Short form

a Completed by caregivers only.

b Completed by persons living with dementia only.

c Actigraphy and sleep diary assessed for two weeks from pre-intervention to the start of Week 1, then from Week 5 to Week 6 (final two weeks of intervention).

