### Reimbursement

Participants will receive an $100 electronic gift voucher upon completion of the final questionnaire and return of actigraph and sleep diary. Participants are provided with a comprehensive list of relevant support services for ongoing support.

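### Weeks 5-6 actigraphs and diaries are returned only after the Week 10 questionnaire, which puts the only on-treatment actigraphy at risk for dyads lost after Week 6

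*Protocol article*

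**What the plan says.** All references are to the protocol article.

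- **Second wear.** Procedure, Intervention subsection: "The actigraphs and new diaries will be posted to be worn again during Weeks 5 and 6 of the intervention". Note c to Table 4 agrees: "Actigraphy and sleep diary assessed for two weeks from pre-intervention to the start of Week 1, then from Week 5 to Week 6". Table 4 marks actigraphy and diary before the intervention and at T2, with nothing at T3.
- **Return after the second wear.** Same subsection: "Sleep diaries and actigraphs are returned following completion of the follow-up questionnaire (Week 10").
- **Return after the baseline wear.** Same subsection: participants wear the device for two weeks and "then return the watches and diaries to the research team to be downloaded and recharged".
- **Payment.** Reimbursement: the $100 voucher is given "upon completion of the final questionnaire and return of actigraph and sleep diary".
- **Use of the data.** Objective sleep by actigraphy is a listed secondary outcome, read together with the diaries. Statistical analysis plans linear mixed models for change in four actigraphy parameters.

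**The concern.** Recording ends at Week 6 and nothing further is recorded on the device, yet the watch and diary stay in the home until the Week 10 questionnaire is done. No measurement reason is given for the wait. The protocol already uses prompt return after the baseline wear, so the route exists. The delay falls on the recording that cannot be repeated.

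Actigraphy has only two windows. A dyad without the second gives no observed within-person change in objective sleep. A mixed model can keep its baseline values, but they carry no direct information on change. Because actigraphy is interpreted with the diary, a diary that does not come back also weakens the actigraphy.

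The voucher adds to this. It requires both the final questionnaire and the return, so a dyad that has decided not to complete T3 has no payment left to gain by sending the device back.

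**Working it through.** The protocol states no figure to reproduce: Sample size gives a convenience sample of 24 dyads without a power analysis, and no loss rate is assumed anywhere. The check has two parts.

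**1. Timing**

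| | Baseline wear | Second wear |
|---|---|---|
| Recording window | two weeks before start | Weeks 5 and 6 |
| Return point | straight after wear | after the Week 10 questionnaire |
| Gap from end of recording to return | none planned | 10 − 6 = about 4 weeks |
| Later actigraphy scheduled | yes (Weeks 5-6) | none |

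Only the second wear has a return that is sequenced after a later assessment.

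**2. Size, as an illustration**

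Inputs:
- n = 24 dyads (Sample size).
- d = share of dyads lost between Week 6 and Week 10. Not in the protocol; assumed 5% to 25%.
- r = share of those lost dyads that still return devices. Not in the protocol; shown at 0, 0.5 and 1.

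Formulas:
- Dyads without a second recording = 24 × d × (1 − r).
- SE multiplier for change, with unchanged SD = √(24 / (24 − dyads without)).

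The comparison is with complete recovery, and assumes no earlier drop-out and no device failure.

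| d | r = 0: dyads without, SE | r = 0.5: dyads without, SE | r = 1 |
|---|---|---|---|
| 5% | 1.2, 1.03 | 0.6, 1.01 | 0, 1.00 |
| 10% | 2.4, 1.05 | 1.2, 1.03 | 0, 1.00 |
| 15% | 3.6, 1.08 | 1.8, 1.04 | 0, 1.00 |
| 20% | 4.8, 1.12 | 2.4, 1.05 | 0, 1.00 |
| 25% | 6.0, 1.15 | 3.0, 1.07 | 0, 1.00 |

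Worked for the worst corner: 24 × 0.25 × (1 − 0) = 6, and √(24/18) = 1.15. For a middle case: 24 × 0.10 × (1 − 0.5) = 1.2, and √(24/22.8) = 1.03.

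If both members of a dyad wear a device, each dyad not recovered removes 2 of 48 second-wear recordings (4.2%).

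**The case against.** The strongest reply is that the protocol states only a planned return point for participants who follow the schedule. A reader might infer that every dyad lost between Week 6 and Week 10 loses its Weeks 5-6 data. The text does not support that. It does not say that a dyad missing T3 keeps the watch, that nobody asks for it back, or that data returned late are discarded. Leaving a questionnaire unanswered is not the same as keeping a study-owned device. The Procedure section adds that "A trained research assistant will manage actigraph recharging and monitor data", and how devices are recovered from non-completers may be set out in a full protocol that the article condenses. This stands: the data are at risk, not known to be lost.

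Three further points also stand.

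- The primary endpoint is feasibility at T2 (attendance, drop-out and the satisfaction score), and none of these depends on device return. The diaries are self-report and are listed in Table 4 under other factors, so only the actigraphy is objective sleep data.
- A reader might infer that the missing recordings would be linked to poor response. That is possible, but nothing in the protocol shows it.
- A reader might infer that return at Week 6 would recover everything. A dyad that disengages near the end of treatment may not post devices then either, and it would still have no voucher to gain if it will not complete T3.

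What the reply does not answer is the delay itself. The late return point is stated text, not a missing detail. A procedure for chasing devices would lower the risk but would not explain why the second wear is handled differently from the first.

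**Conclusion.** The point holds as an avoidable exposure of secondary data. The stated schedule makes planned recovery of a T2 secondary outcome follow T3, for no stated measurement purpose, and the voucher rule gives a dyad that skips T3 no payment for returning the device.

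The size cannot be fixed from the protocol. Over the assumed loss range, the result runs from no effect, if every lost dyad returns its devices, to a quarter of the dyads without a second recording, if none does. Values near the upper end need both high late attrition and no device recovery. The effect would be on the precision, and possibly the representativeness, of the objective sleep change; the feasibility conclusion does not rest on it. The case for acting is that the remedy is cheap, not that a large loss has been shown.

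**What to change.** In Procedure, Intervention subsection, replace the sentence on return after Week 10 with a rule that second-wear actigraphs and diaries are posted back at the end of Week 6, by the route used after the baseline wear, and downloaded on receipt. Keep the voucher payable after T3, so the incentive to complete the Week 10 questionnaire remains.

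The change moves the date of a posting that already takes place and adds no assessment. Devices become free about four weeks sooner, and queries about the recordings can be raised closer to the nights concerned.

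Cost: the same subsection requires ethics approval before a modification is implemented, participant instructions must be revised, and a Week 6 reminder is needed. Trial status describes data collection as ongoing, so the change can apply only to dyads not yet past Week 6, and the sample would contain two return procedures.

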### Community and consumer involvement

Authors AP and TV are community advisors with lived experience of dementia and caregiving respectively, and hold vast experience and expertise in advisory and research collaboration. Community advisors are heavily involved in all stages of project development and provide input on (but not limited to): explanatory statements and consent forms, study design, informed consent procedures, development and delivery of focus groups and interviews, intervention materials, language recommendations, questionnaire content and aesthetics, recruitment methods, promotional materials, and other consumer-facing content.

In late 2021, two focus groups (one for caregivers and one for people with dementia [*n* = 3 each group]), and five semi-structured interviews were undertaken to: (a) identify common sleep and daytime changes; (b) identify helpful/unhelpful strategies for sleep and daytime effects; (c) explore barriers to help-seeking; (d) seek feedback and recommendations on proposed study design, intervention content, logistics, and predicted feasibility. Qualitative and quantitative feedback arising from focus groups and interviews were documented in a tracking sheet and incorporated in the development of the intervention. Suggestions included a mix of dyadic and small group delivery, weekly sessions of 90 min duration, focusing content on resourcing caregivers, and making it optional for the person living with dementia to attend (manuscript currently in preparation; [name], [name], [name], [name], [name], [name], [name], [name], [name], [name], [name], [name], 2023, unpublished data).

### Intervention

The intervention delivery has two components: (1) weekly therapist-led personalised and group sessions delivered *via* video conferencing over six weeks; and (2) a hardcopy 37-page participant workbook (see Supplementary). The workbook includes a reflective journal and contains a list of resources to support participants’ learning and application of new skills and promote adherence.

The intervention will be delivered by registered psychologists with expertise in the provision of sleep interventions under the supervision of a clinical psychologist with experience working with people living with dementia and caregivers. The lead intervention developer (SV) holds experience in the design, development and delivery of sleep-based interventions, and undertook additional training in dementia awareness, and caregiver sleep and wellbeing to assist content development. Manualised scripts for each session were developed to ensure consistency.

The intervention content is multi-modal and draws from CBT for insomnia, mindfulness, physical activity interventions and light therapy. Different components include: collaborative goal-setting, psychoeducation, practical sleep strategies based on stimulus control and sleep hygiene, relaxation strategies (*e.g.*, deep breathing, mindfulness), physical activity recommendations (*e.g.*, walking, gardening, stretching), gaining natural light during the morning/daytime and avoiding bright light at night, prioritising rest and self-care, enlisting support from others, and strategies to manage fatigue (*e.g.*, planning, pacing, taking breaks).

The intervention adopts a “toolkit” approach based on feedback arising from community consultation, in which dyads learn of several strategies and select to use those that suit their unique, and often changing, circumstances. Intervention providers take a validating, non-judgemental, supportive, and motivational stance to encourage and empower participants to make changes in their everyday lives; these therapeutic qualities were identified through community consultation as being particularly salient given the unique needs of the study population. The intervention components were designed to upskill caregivers in addressing their own sleep and daytime concerns while supporting sleep in the person they care for, however some components (*e.g.*, relaxation, physical activity) were designed to concurrently apply to both caregivers and people living with dementia. Caregivers will be invited to attend all sessions with optional attendance for people living with dementia (except Session 5 which is offered specifically to caregivers following recommendations from community consultation).

Participants will attend six sessions in total (see Table 3). All sessions will run for up to 90 minutes except for Session 4 (45 minutes). Sessions 1 and 4 will involve individual dyads while remaining sessions (*i.e.,* Sessions 2, 3, 5 and 6) will be delivered in small groups with no more than four dyads (or caregivers in Session 5). Session 1 will be framed as an “orientation” to the project which aims to: (a) identify current sleep concerns and collaborate on personalised goals for the project; (b) provide participants psychoeducation on sleep and insomnia, and provide key sleep strategies; (c) offer recommendations based on identified goals and; (d) discuss ways of overcoming barriers to encourage adherence, including use of the workbook. Participants receive all core components of the intervention however components specifically relevant to the dyad in light of their unique circumstances and goals are highlighted, thus *personalising* the intervention. For example, relaxation strategies may be discussed for a dyad in which sleep onset difficulties are a reported priority, or fatigue management strategies for another dyad that identifies the goal to feel less fatigued during the day.

Group sessions will generally include: (a) an initial review of the previous session and time to answer questions; (b) psychoeducation of key concepts and strategies specific to each session and; (c) guided discussion to enable sharing and collaboration, and reference to relevant sections of the workbook. The purpose of Session 4 is to provide a personalised check-in to encourage engagement and adherence, answer any questions and collaborate a plan for the remaining period of intervention.

**Table 3 table-3:** Outline of personalised and group sessions.

**Session 1**	**Introduction (Individual dyads)**
	Acknowledgement of Country Overview of project Psychoeducation: • Typical sleep changes in people living with dementia and caregivers • Sleep deprivation vs insomnia • “3 ingredients for good sleep”—sleep drive, circadian rhythm, quiet mind Cognitive behavioural strategies for insomnia: • Stimulus control (*e.g.*, only going to bed when sleepy, getting out of bed if stimulated and unable to sleep) • Anchoring wake time • Guidance on napping • Sleep hygiene Collaborative goal-setting, motivational interviewing, personalising strategies Workbook exercises
**Session 2**	**Light, Night and Exercise (Group Session)**
	Introduction (including Acknowledgement of Country, group guidelines) Psychoeducation: • Circadian rhythm and sundowning • Role of light and exercise on circadian rhythms (including blue light) • Effect of light at different times of day/night Light therapy strategies: • Natural light exposure upon awakening and during daytime • Avoidance of bright lights at night (using lamps, dim lights) • Guidelines on electronic device use Psychoeducation: • Exercise and sleep, physical and mental health Encouraging physical activity (*i.e.,* 30 min of physical activity a day) Group discussion (implementing light and night strategies into daily routine) Workbook exercises
**Session 3**	**Self-care and Relaxation (Group Session)**
	Brief Q&A time Psychoeducation: • Self-care • Normalising stress and worries in caregivers and people living with dementia Enlisting formal/informal supports Group discussion (identifying relaxation strategies) Mindfulness: • Experiential deep breathing and body scan Relaxation strategies: • Worry journal • Self-talk Identifying prompts/cues to encourage adherence (*e.g.*, hand-written notes) Guidance for nighttime awakenings (for caregivers) Group discussion (implementing relaxation exercises into routine, reminders) Workbook exercises
**Session 4**	**Check In (Individual dyads)**
	Discussion of changes in sleep and wellbeing Review of goals set in Session 1 Identifying helpful/unhelpful strategies Identifying and collaboratively addressing barriers to engagement Personalised planning and goal-setting
**Session 5**	**Managing Fatigue (Group Session—Caregivers only)**
	Brief group discussion of relaxation strategies Psychoeducation: • Fatigue and components • Normalising fluctuations in energy levels • Fatigue vs sleepiness Self-monitoring energy levels (mobile phone analogy) Fatigue management strategies: • Plan, pace and prioritise tasks • Taking breaks • Keeping realistic expectations • Enlisting social support • Engaging in a ‘daily joy’ Group discussion (self-monitoring, identifying and addressing potential barriers to engagement)
**Session 6**	**Review and Beyond (Group Session)**
	Review of previous session content Group discussion (reflections of project, strategies and challenges) Relapse prevention: • “Traffic light” analogy (green, amber and red zones of wellbeing) • Self-monitoring and identifying early warning signs • Contingency planning for challenging times Group discussion—self-monitoring, planning Thank you and farewell

Group guidelines will be discussed during Sessions 1 and 2 and reiterated in the workbook (See Supplementary). Community advisors will be invited to attend sessions to provide recommendations for intervention providers to promote respectful and sensitive delivery. All sessions are video-recorded and offered to dyads unable to attend sessions, and for researcher training purposes.

